### Sample size calculation

This is a feasibility study, and therefore a formal sample size calculation is not required. However, preliminary data from this stage will be used to determine the sample size required for a future definitive study. Whitehead *et al* (2016) suggested that a sample size of 10 per treatment arm in the pilot phase would provide enough preliminary data to determine the sample size needed to detect a medium effect in a full interventional trial.^44^ While this study is not interventional, we believe the principles to be transferable, and therefore, we will aim to recruit 40 study participants, with 10 in each group.

### Statistical analysis

The primary aim of the ACE-MAP study is to assess the feasibility and acceptability of the proposed study procedures. Recruitment feasibility will be assessed per stream by calculating the overall recruitment rate (number of participants successfully recruited to the study per week) and the recruitment proportion (number of participants successfully recruited to the study divided by the number of potential participants approached). Acceptability will be assessed with a modified version of an acceptability questionnaire developed by Sekhon *et al*^43^ administered to study participants at the end of the assessment session. The data will be presented as counts and proportions, with free-text comments presented as either themes or original anonymised quotes.

The secondary aim is to generate preliminary data to understand the impact of ACEs on QST thresholds in people with multimorbidity and/or chronic pain. Descriptive statistics will be generated on all groups of data (demographics, LTCs, chronic pain, ACEs, medication and QST parameters). We will perform exploratory analyses, such as investigating the association between the number of ACEs experienced and individual QST parameters, and how these relationships vary based on multimorbidity/chronic pain status, using a range of statistical techniques (eg, χ^2^ tests, Student’s t-tests, regression analysis). These analyses will inform the project design and sample size calculation for a subsequent definitive study.

All statistical analyses will be performed in R V.4.2.2 using the RStudio integrated development environment (RStudio Team, Boston, USA).

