**Methods and analysis:**

We plan to recruit 40 participants, with 10 in each of the following groups: (1) chronic pain with multimorbidity; (2) chronic pain without multimorbidity; (3) multimorbidity without chronic pain; and (4) controls. Participants will complete a series of questionnaires (including on ACEs, chronic pain and long-term conditions) and will then take part in QST assessments. The primary study outcomes will include measures of feasibility and acceptability of the proposed study design. The secondary study outcomes will include exploratory analysis on the relationship between ACEs and QST thresholds.

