### Procedure

Potential participants will be provided with a participant information sheet by email or post (depending on individual preference) prior to attending for their assessment session. They will be given at least 24 hours to consider their participation and will have the opportunity to ask questions (via email or telephone) prior to the session.

Written informed consent will be obtained at the start of the assessment session, prior to the completion of any study assessments.

Next, participants will complete a series of questionnaires on:

Demographics, including year of birth, sex assigned at birth, ethnicity, recruitment stream, Scottish Index of Multiple Deprivation, level of education, employment status and household income.Health behaviours, using the General Practice Physical Activity Questionnaire^38^ and the WHO’s Alcohol, Smoking, and Substance Involvement Screening Test.^39^Long-term conditions, using the LTCs listed in table 1.Chronic pain, using the UK Biobank Pain Web Questionnaire.^40^Adverse childhood experiences, using the CAPE ACE questionnaire (in the final stages of development).Current medication.

Then participants will have their height and weight recorded.

Next, we will begin QST based on a protocol devised by the German Research Network on Neuropathic Pain,^41^ with the addition of a conditioned pain modulation (CPM) paradigm. Each test will be performed bilaterally, with the exception of the CPM test, which will be performed on one side only.

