
Finally, participants will complete a questionnaire on study acceptability, using a questionnaire adapted from Sekhon *et al*.^43^

There is no planned follow-up for this study.

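### Acceptability, a primary outcome, rests on a form given as the last step of one session, with no stated provision for participants who consent but stop early

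*Protocol article*

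**What the plan says.** All references are to the protocol article.

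- The Abstract makes acceptability a primary outcome: "The primary study outcomes will include measures of feasibility and acceptability of the proposed study design".
- Statistical analysis gives one way of measuring it, a modified published questionnaire "administered to study participants at the end of the assessment session". On the summary it says: "The data will be presented as counts and proportions". Free-text comments are reported alongside. It does not say what the proportions are proportions of.
- Procedure puts the form after the questionnaires, the sensory tests and the cold water bath: "Finally, participants will complete a questionnaire on study acceptability". It then adds: "There is no planned follow-up for this study".
- Procedure also fixes the point of consent: "Written informed consent will be obtained at the start of the assessment session, prior to the completion of any study assessments".
- The two recruitment measures in Statistical analysis are a rate ("number of participants successfully recruited to the study per week") and a proportion ("number of participants successfully recruited to the study divided by the number of potential participants approached").

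**The concern.** A form given last is reached by those who stay to the end. Before it come questions on childhood adversity, which the Ethics and dissemination section itself recognises may distress some participants, and then a mostly bilateral set of sensory and pain tests and the cold water bath. Finding the session unacceptable is one reason a person might leave before that point. If so, whether an answer is missing depends on what the answer would have been, and the proportion among returned forms leans towards acceptance.

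No other stated primary measure would show this. The recruitment measures can be satisfied once a person has consented, and neither changes if that person leaves part-way. Time in the water bath reflects tolerance of one test, is observed only in people who get that far, and is not named as an acceptability measure.

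At stake is the primary aim. The study is meant to show whether these procedures can be carried into a definitive study, and with 10 people per group one or two unrecorded departures can change how a group looks.

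**Working it through.** **Inputs from the article**
- Planned number: 4 groups × 10 = 40, which agrees with Sample size calculation.
- Timing of the form: the last step of the only session (Procedure and Statistical analysis agree).
- Later contact: none planned (Procedure).
- Consent: before any assessment (Procedure), so a person who stops early is already a participant.
- Early-stop rate, acceptability target and denominator: not given.

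**Assumptions for illustration**
- Acceptability is reduced to one yes/no answer. The article does not define it this way.
- *d* of the 40 stop early and return no form; *x* of the 40 − *d* finishers find the session acceptable.
- Every person who stops found it unacceptable. This is the worst case and is relaxed below.

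**Formula**

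Proportion among finishers: q = x/(40 − d). Proportion among all consented: x/40. The difference is x/(40 − d) − x/40 = q × d/40.

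**Results with about 95% of finishers accepting**

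| Early stops | Finishers only | All consented | Difference q × d/40 |
|---|---|---|---|
| 0 | any q | same q | 0 |
| 2 | 36/38 = 94.7% | 36/40 = 90.0% | 4.7 points |
| 4 | 34/36 = 94.4% | 34/40 = 85.0% | 9.4 points |
| 6 | 32/34 = 94.1% | 32/40 = 80.0% | 14.1 points |

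For 4 stops, the exact 95% intervals are 81% to 99% (34/36) and 70% to 94% (34/40). They overlap widely. The issue is a shift in one direction, not a difference that a study of this size could detect.

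**Relaxing the worst case, with 4 stops**
- All four found it unacceptable: 34/40 = 85%.
- Two did, and two left for unrelated reasons and would have accepted it: (34 + 2)/40 = 90%.
- None did: (34 + 4)/40 = 95%, against 94.4% among finishers, so there is no overstatement.

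**Within one group of 10**

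Two stops and no complaint from finishers give 8/8 = 100% against 8/10 = 80%.

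**Chance that the question arises at all**

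P(at least one stop in 40) = 1 − (1 − r)^40. For an assumed r = 2% this is 1 − 0.98^40 = 55%; for r = 5% it is 1 − 0.95^40 = 87%.

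**The case against.** A reader might infer that the plan bars early stoppers from the form and removes them from the denominator, so that survivor bias in the primary outcome is established. The article does not support that. It says participants get the form when the session ends. A person who stops is still a participant, and their session arguably ends when they stop, so staff could hand them the form without departing from the text. The denominator is simply not named. Finishers-only is a natural reading of questionnaire proportions, but it is an inference.

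A reader might also infer that the missing answers would come mainly from people with chronic pain or high adversity scores. That is plausible, but nothing in the article shows it.

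Other points against the concern also stand:
- The stop rates and the yes/no scoring are assumed, and no acceptability threshold is stated, so no decision is shown to change.
- Failing to tolerate a test is not the same as leaving. Pain threshold tests end at the participant's own report, and time in the water bath is recorded up to its maximum, so such a person can still reach the form.
- Participants have at least 24 hours with the information sheet, and the patient group reviewed burden.

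The strongest objection is that handling of withdrawals belongs in the full protocol, which is not shown. That would settle the matter if the article were merely silent. It is not: it fixes the form as the last step in two sections, rules out planned follow-up, and chooses recruitment measures that do not register completion. The full protocol may qualify this, in which case one sentence would resolve it.

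**Conclusion.** The point holds in a limited form. The stated timing, with no follow-up and no completion measure, leaves no provision for the form to reach a consented participant who stops early, while that person can still count as recruited. The reported acceptability may therefore be too favourable.

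The size cannot be derived from the article. It is zero if nobody stops, or if those who stop would have answered much as finishers did. In the illustrated worst case it is about 5, 9 or 14 percentage points for 2, 4 or 6 stops among 40. These figures assume that proportions are taken over returned forms and that every stopper found the session unacceptable. Even with 40 as the denominator, the stoppers' reasons and comments would be lost.

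The change is worth making because it protects a primary outcome at almost no cost. It does not show that the outcome will be biased.

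**What to change.** 1. State that the existing acceptability form is offered to every consented participant whenever their session ends, complete or not, with a voluntary email or postal version for anyone who prefers to leave at once.
2. Report the number of early stops, and the point at which they occur, by group as a feasibility measure beside the recruitment rate and proportion.
3. Present acceptability with all consented attenders as the denominator and show non-returned forms as their own category. A worst-case count that treats them as not acceptable is optional.

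The cost is a change of wording and a small handling rule for a form that already exists. The reported proportion may come out slightly less favourable.

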### Ethics and dissemination

Ethical approval for the ACE-MAP study was granted by the National Health Service Scotland B Research Ethics Committee (reference: 24/SS/0031). ACEs are a sensitive and potentially triggering subject, and so care will be taken to ensure participant safety. The ACE questionnaire that we will use is based on the WHO’s Adverse Childhood Experiences International Questionnaire^45^ and has been adapted by CAPE with detailed input from our patient and public involvement group. This included ensuring that the questionnaire wording is respectful, acceptable to people who have experienced ACEs (and those who have not) and that a broad and relevant range of ACEs are covered to reflect a range of backgrounds. Our patient and public involvement group highlighted the need to signpost to organisations that can provide additional support; these details will be offered to each participant.

The ACE-MAP study has been registered in the ISRCTN registry (ID: ISRCTN10049430). It will be conducted in compliance with the principles of the Declaration of Helsinki (2013) and Good Clinical Practice.

Results from the study will be presented at scientific conferences, published in a peer-reviewed journal and shared with patients and members of the public through other media streams.
